#### Secondary outcomes

##### Health behaviours

Device-measured sedentary time and sleep will also be assessed using the Axivity AX3 tri-axial accelerometer. Sleep periods will be detected using the Van Hees et al. heuristic [41].Self-reported physical activity will also be assessed. The Active Australia Survey provides contextual physical activity information as it assesses the frequency and duration (in minutes per week) of walking for transport, walking for recreation, moderate physical activity and vigorous physical activity [42]. The Active Australia Survey has acceptable test–retest reliability and validity in the Australian adult population and has been documented as a useful evaluative tool for detecting intervention related change in physical activity [43, 44].Self-reported sitting time will be measured using the 10-item ‘Workforce Sitting Questionnaire’ [45]. All participants will report time (hours/minutes) spent sitting on usual working and non-working days in relation to work, transport, TV use, computer use and other leisure-time sitting. One question also measures the number of days participants usually work in a week. This survey has demonstrated adequate test–retest reliability and validity [45].Self-reported sleep behaviour will be assessed using items from both the Behavioural Risk Factor Surveillance Screening Sleep Module [46] and the valid and reliable Pittsburgh Sleep Quality Index [47]. This study assesses average hours of sleep obtained, snoring behaviour, unintentionally falling asleep during the day, nodding off while driving, whether one feels rested and levels of sleep quality. Additionally, an objective measure of sleep will be collected using the Axivity accelerometer. Total sleep time, sleep efficiency, number of awakenings, sleep onset and sleep offset will be extracted from the accelerometer data using established protocols [39].

##### Work-related outcomes

The Health and Work Questionnaire (HWQ), a survey for assessing workplace productivity, consists of 24 items, with each item rated on a 10-point Likert scale (e.g. ‘very dissatisfied’ to ‘very satisfied’) [48]. The questions assess work quality, quantity and efficiency, as well as impatience, concentration/focus, work satisfaction and non-work satisfaction. The HWQ shows very good internal consistency reliability [48].The World Health Organization’s Heath and Work Performance Questionnaire (HPQ), will be used to assess absenteeism and presenteeism [49]. Eight items are used to assess absenteeism and 3 items are used to assess presenteeism. Good concordance was found between the HPQ and other productivity indicators [49].The Maslach Burnout Inventory will assess various aspects of burnout syndrome [50]. It has a total of 22 items that are scored on 7-point scales and contains 3 subscales: emotional exhaustion, depersonalisation and personal accomplishment. Various psychometric analyses showed that the scale has both high reliability and validity as a measure of burnout [50].The Employee Wellbeing Scale: This survey, with demonstrated validity and reliability [51], assesses employee wellbeing using 18 items on 7-point Likert scales (scored: 1 = strongly disagree; 7 = strongly agree). The survey assesses wellbeing across three dimensions: life wellbeing, work wellbeing and psychological wellbeing.

##### Mental health and quality of life

Quality of life will be measured through the Short-Form Health Survey (SF-12) which includes questions on physical and mental health. The SF-12 is widely used, valid and reliable [52].Depression, anxiety and stress: The 21-item Depression, Anxiety and Stress Scale (DASS21) will be used to assess mental health outcomes [53]. The DASS21 provides a quantitative measure of distress symptom severity; it is not a measure of clinical diagnosis. Three 7-item subscales measure depression, anxiety and stress. These scales have demonstrated acceptable validity and reliability in community samples of adults [53].The Satisfaction with Life Scale is a 5-item measure of an individual’s global evaluation of their life [54]. Participants complete the measure on a 1 to 7 Likert-type response scale. Scores can range between 5 and 35, with higher scores indicating greater life satisfaction. The scale has been widely used, with high reliability and validity [55].The Positive and Negative Affect Schedule—short form (I-PANAS-SF) is a 10-item Positive and Negative Affect Scale [56]. The scale measures an individual’s experiences of positive and negative affect with two 5-item subscales. Participants complete the measure on a 1 to 5 Likert-type response scale. Scores can range between 5 and 25 for each subscale, with higher scores indicating greater experience of positive or negative emotion. The scale is reliable, valid and has demonstrated cross-cultural validity [57].Habit strength will be assessed using the 4-item Self-Reported Behavioural Automaticity Index [58], which is a subscale of the Self-Reported Habit Index [59]. Participants are asked to what extent they agreed with the items, ‘Physical activity is something I do… (1) automatically, (2) without having to consciously remember, (3) without thinking, (4) before I realise I’m doing it’, using response scales from 1 (strongly disagree) to 7 (strongly agree). The habit strength score is calculated as the mean of the 4 items. This scale was found to be reliable and sensitive to the effects of habit on behaviour [58].

##### Intervention use and usability

App usability and usefulness: The overall usability of the app will be investigated using the System Usability Scale [60]. This 10-item scale has demonstrated acceptable reliability and validity for measuring the usability of websites and apps [60]. Additionally, there will be 5 items on how useful participants found the app in supporting them in becoming more active. These outcomes will only be measured at the 3-month time point.App usage statistics: App usage will be measured using the Google Analytics Firebase traffic analysis platform (Alphabet Inc, Mountain View, CA), as well as by monitoring user-generated content. Features monitored will include (but are not limited to) the number of times the app was opened, time in the app, app pages visited, number of action plans completed, number of completed conversations, questions asked in chat, amount of nudge feedback provided, physical activity recorded through the app (i.e. activity minutes and steps) and activity milestones achieved (e.g. times the daily goal was met). App usage will be monitored for the entire study duration.

##### Demographics

The following demographic factors will be assessed: age, sex, weight, height, marital status (single, widowed, divorced, separated, married, in a relationship), ethnicity (Caucasian, Aboriginal or Torres Strait Islander, African, Asian, other), number of years of education, occupational category (e.g. manager, professional, sales), income, postcode, residential environment (e.g. rural area), Accessibility/Remoteness Index of Australia (ARIA) [61] and presence of chronic diseases (e.g. hypertension, stroke, arthritis, depression). Additionally, alcohol consumption will be assessed using the Alcohol Use Disorders Identification Test (AUDIT-C). It is a 3-item test for heavy drinking and/or active alcohol abuse or dependence, with demonstrated validity and reliability [62]. Smoking will be assessed using a single item to classify participants as either a current smoker or non-smoker. Diet will be assessed using four items that evaluated the daily frequency of fruit and vegetable consumption and the number of times soft drinks and fast foods were consumed in the previous 7 days [63]. An overview of all measures and when they are being assessed is provided in Table 2.

**Table 2 Tab2:** Overview of measures, instruments and when they are being assessed

Measure	Instrument	Timepoints	Groups
In- and exclusion criteria	Eligibility survey (includes informed consent for those eligible)	During recruitment	All those interested
Sample characteristics	Demographic questions [61, 63], AUDIT-C [62]	Baseline	All (i.e. intervention and control groups)
Physical activity	Axivity AX3 accelerometer [36–40]	All (i.e. baseline, 3 months and 6 months)	All
	Active Australia Survey [42–44]	All	All
Sitting time	Axivity AX3 accelerometer [36]		
	Workforce Sitting Questionnaire [45]	All	All
Sleep	Axivity AX3 accelerometer [36, 41]		
	BRFSS Sleep Module [46]	All	All
	Pittsburgh Sleep Quality Index (PSQI) [47]	All	All
Workplace productivity	Health and Work Questionnaire (HWQ) [48]	All	All
Absenteeism and presenteeism	World Health Organization’s Heath and Work Performance Questionnaire (HPQ) [49]	All	All
Burnout	Maslach Burnout Inventory [50]	All	All
Wellbeing	Employee Wellbeing Scale [51]	All	All
Quality of life	Short-Form Health Survey (SF-12) [52]	All	All
Mental health	Depression, Anxiety and Stress Scale (DASS21) [53]	All	All
Satisfaction	Satisfaction with Life Scale [54, 55]	All	All
Affect	Positive and Negative Affect Schedule—short form (I-PANAS-SF) [56, 57]	All	All
Habit strength	Self-Reported Behavioural Automaticity Index (SRBAI) [58, 59]	All	All
App usability and usefulness	System Usability Scale and custom questions [60]	3 months only	Intervention group only
App usage statistics	Google Analytics and app database	Continuous throughout the 6-month intervention period	Intervention group only

### Sample size

Sample size for the study is based on the primary outcome of change in device-measured MVPA (min/day). Several reviews of app-based physical activity interventions suggest that most studies have small to medium effects on change in physical activity and have high dropout rates, up to approximately 30% [64, 65]. Hence, to detect a small to medium difference in the change in daily MVPA between groups (*d* = 0.45; corresponding with a minimal detectable difference of 10 min/day), at the study’s primary time point of 6 months, 76 participants per group will be required to achieve 80% power using an alpha level of 0.05. The number of participants per group will be inflated by 30% (99 participants per group) to account for drop out. Hence, a total of 198 participants will be recruited into the RCT.

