## Methods

### Trial design

The MoveMentor trial is a parallel group, two-arm, superiority trial with a 1:1 allocation ratio to investigate the effectiveness of an app-based digital assistant to increase physical activity compared to a no intervention control group. Given the novelty of the intervention, we first need to establish the effectiveness of the intervention against a true control group, prior to comparing it to alternative interventions. The control group will be offered access to the intervention after the final assessment has been completed. The study setting is ‘home-based’, as there will be no face-to-face contact with participants, and all communication will occur via e-mail or phone. Primary and secondary outcomes will be assessed at baseline, 3 months and 6 months. The study has received ethics approval from the Human Research Ethics Committee (HREC) of the Central Queensland University (0000024786) and complies with the Helsinki Declaration. While not anticipated, any adverse events will be reported immediately to the HREC and managed according to their instructions and reported in publications resulting from this study. Likewise, ethical approval will be sought prior to any protocol amendments should they be needed. The Central Queensland University is the sponsor for this trial. There are no plans to use participants’ data in any other studies. This study protocol has been prepared in accordance with SPIRIT guidelines (see Additional file 1 and Table 1) and study outcomes will be reported according to CONSORT guidelines [25, 26].

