## Discussion

The current trial presents a unique opportunity to study the effectiveness of a new generation of digital interventions that use reinforcement learning (i.e. contextual bandit) in combination with real-time data to deliver a highly personalised app-based digital assistant for promoting physical activity [23]. By addressing the limitations of existing conversational agents and applying advanced machine learning techniques, we aim to pave the way for more effective and adaptable interventions. There is an ongoing proliferation of health and physical activity smartphone apps, yet very little work has been carried out to study the utility and effectiveness of these population-targeted apps [68]. Soon, many more of these apps will also be applying various form of machine learning techniques to influence health behaviour. As such, our work will contribute to understanding how effective these approaches are, and what potential downsides might be. We expect that the current study’s findings will provide increased insights into the benefits of applying machine learning in engaging and retaining participants in app-based interventions, something previous interventions have struggled with [69, 70]. Higher participant engagement and retention have been shown to result in higher levels of behaviour change, and ultimately this will lead to improved health outcomes [70].

There are several strengths to this trial; for example, our trial will have more participants and measure intervention outcomes over a longer period than most comparable interventions in this space [18–21]. Additionally, our trial applies a robust study design, rigorous participant screening, device-measured physical activity outcomes, numerous measures to assess secondary outcomes, standardised exposure and contact across groups, and sufficient analytical power to observe between group changes. The lack of face-to-face contact with participants aligns with the nature of real-world digital interventions and allows the recruitment of participants anywhere in Australia, which enhances the generalisability of the study findings. However, a potential downside of this is a lower feeling of accountability towards study participation and higher levels of attrition. Nevertheless, this study and the intervention it aims to evaluate are well-positioned to generate new knowledge and advance the field in this space.

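### The 30% dropout allowance was multiplied (76 × 1.3 = 99) instead of divided (76 / 0.7 = 109), so power at 30% loss is about 75%, not the stated 80%

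*Protocol article*

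**What the plan says.** The Sample size section of the protocol article bases the calculation on the between-group difference in change in daily moderate-to-vigorous physical activity (MVPA), "at the study’s primary time point of 6 months". The effect size is d = "0.45; corresponding with a minimal detectable difference of 10 min/day". On that basis, "76 participants per group will be required to achieve 80% power using an alpha level of 0.05".

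On attrition, the section cites reviews of app-based activity interventions, whose studies "have high dropout rates, up to approximately 30" per cent. No other dropout rate is given. The allowance follows: "The number of participants per group will be inflated by 30% (99 participants per group) to account for drop out". The section ends: "Hence, a total of 198 participants will be recruited into the RCT".

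The Discussion lists "sufficient analytical power to observe between group changes" among the strengths of the trial.

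**The concern.** The section names a required number of evaluable participants and a loss rate, then gives a recruitment target that does not connect the two. Adding 30% to the required number is not the same as allowing for a 30% loss from the recruited number. A loss of 30% from 99 leaves fewer than 76.

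This is the power statement for the primary outcome at the primary time point. If it goes unchanged into the results paper, a null 6-month result will be read as coming from a trial with 80% power for 10 min/day at up to 30% loss, which the design did not provide.

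**Working it through.** **Inputs**, from Sample size unless noted:
- d = 0.45, equated with 10 min/day, so the implied SD is 10 / 0.45 = 22.2 min/day
- alpha 0.05, target power 80%
- 76 per group evaluable, 99 per group recruited, 198 in total
- dropout up to about 30%
- design: "two-arm, superiority trial with a 1:1 allocation ratio" (Trial design)
- sidedness is not stated. Two-sided is assumed, because a one-sided test needs only 62 per group and does not match 76.

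**Step 1. Reproduce the 76.** With n per group = 2 × ((1.960 + 0.842) / d)²:
- d = 0.45 gives 77.5, so 78. The t-test version gives 78.5, so 79.
- d = 10/22 = 0.4545, which prints as 0.45, gives 75.98, so 76.

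The stated 76 is therefore recovered if the SD was taken as 22 min/day and d was rounded for print. With d = 0.45 exactly, 76 per group gives 79.2% (normal) or 78.7% (t).

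**Step 2. Reproduce the 99.** 76 × 1.30 = 98.8, rounded up to 99; 2 × 99 = 198. This matches exactly, so the allowance was applied by multiplication.

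**Step 3. Apply the 30% loss to the recruited number.**
- 99 × 0.70 = 69.3 per group remain, against 76 required: 76 − 69.3 = 6.7 short.
- Recruitment that retains 76: 76 / (1 − 0.30) = 108.6, so 109 per group and 218 in total. That is 218 − 198 = 20 more than planned.

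**Step 4. Power with what remains** (two-sided alpha 0.05):

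| Evaluable per group | d | Normal | t-test |
|---|---|---|---|
| 76 | 0.45 | 79.2% | 78.7% |
| 76 | 10/22 | 80.0% | 79.5% |
| 69 | 0.45 | 75.3% | 74.7% |
| 69 | 10/22 | 76.1% | 75.5% |
| 69.3 | 0.45 | 75.5% | 74.9% |
| 69.3 | 10/22 | 76.3% | 75.7% |

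The range at 30% loss is 74.7% to 76.3%. At d = 0.45 by t-test, the fall from 80% splits into 78.7 − 74.7 = 4.0 points from the dropout step and 80 − 78.7 = 1.3 points from 76 being slightly low for that d.

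**Step 5. Difference detectable with 80% power at 69 per group.** The t-test gives d = 0.480 and the normal formula d = 0.477. With SD 22.2 these are 10.7 and 10.6 min/day; with SD 22 they are 10.6 and 10.5 min/day. The plan states 10.

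**Step 6. Loss at which the stated power survives.**
- To keep 76: 1 − 76/99 = 23.2%.
- To keep 79 (t-test at d = 0.45): 1 − 79/99 = 20.2%.

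**The case against.** There are four arguments for leaving the text alone.

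- **The 30% is an upper figure from other trials, not this trial's expected loss.** That is fair, and the power statement has to be conditional on it: at 23% loss or less, 76 per group are retained. But it is the only dropout figure in the section, and it is the one the allowance was built on. The Discussion itself warns that the lack of face-to-face contact may raise attrition. Primary outcome data must also meet the valid-wear criterion (Primary outcome section), so invalid wear can add to loss at 6 months; the article gives no rate for it.
- **The 76 is not an error.** This stands. It reproduces at d = 10/22, so the gap between 76 and 78 or 79 is most likely rounding. It accounts for only about 1 point and is a side note.
- **The mixed model and multiple imputation can use partial data.** They may recover some information from participants lost after 3 months, so a completers-only power figure may be somewhat pessimistic for the planned analysis. The sample size calculation takes no credit for this and gives no correlation to support it. It also cannot explain 99, which is exactly 76 × 1.3.
- **The Discussion phrase carries no number, and a null result will be judged on its confidence interval.** Both are true, and they limit how much the point matters. The explicit 80% in Sample size is still not delivered at the loss rate named beside it.

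**Conclusion.** The concern holds. The allowance was multiplied where it should have been divided, and 99 per group does not cover a 30% loss. At that loss, about 69 per group remain and power for d = 0.45 is about 75%, against the stated 80%. Equivalently, 80% power applies to about 10.7 min/day rather than 10.

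This rests on a two-sided 5% test of two means, analysis of those evaluable at 6 months, and loss at the top of the cited range. It does not depend on whether the normal or t formula is used, or on whether d is 0.45 or 10/22. The shortfall disappears if loss is no more than about 20% to 23%.

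The practical weight is modest: about 4 points of power from the dropout step and about 5 against the stated figure. Nothing in the conduct or analysis of the trial is invalidated, but the sample size statement is wrong as written and should be corrected.

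**What to change.** The Trial status section says recruitment was completed on 25 November 2024, so the remedy is to correct the statement, not to enlarge the trial. In Sample size, replace the sentence on the allowance with wording such as:

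*A recruitment target of 198 (99 per group) gives about 75% power for d = 0.45 (10 min/day) if 30% are lost by 6 months, or 80% power for d = 0.48 (about 10.7 min/day). Power of 80% at d = 0.45 holds only if loss is at most about 20% to 23%.*

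State that the test is two-sided, and give the SD behind d so that the 76 can be reproduced. Make the Discussion's power claim conditional in the same way. The article does not give the number actually enrolled, so the results paper should report the number randomised and the 6-month retention alongside the design power.

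The cost is two edited sentences and a slightly less favourable stated power. No extra participants and no change to the analysis are needed.

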### Statistical analyses

Data will be analysed by a statistician blinded to group allocation, using generalised linear mixed models (GLMM), including fixed effects for group, time, the group-by-time interaction and a random subject effect [66]. GLMM analyses examine changes from baseline to each follow-up time point for each intervention group compared to the control group while accounting for within-person nesting of variables across time [66]. Random effects mixed modelling will also be used to explore potential changes in secondary outcomes. Planned subgroup analyses include examining any moderating effects of sociodemographic variables (e.g. sex, age, income) and app usage as potential mediator for increases in physical activity levels. Data will be tested for linearity and normality to ensure the proper statistical techniques are applied. The most appropriate approach to handling missing data will be applied depending on the pattern and amount of the missing data. However, if possible, intention-to-treat including all participants with valid baseline data and multiple imputation by chained equations will be used to handle missing data [67]. The analyses will be conducted using SPSS v30.

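### The primary model is valid but compares change scores; a common baseline mean, or baseline MVPA as a covariate, would sharpen the 6-month contrast without new data

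*Protocol article*

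**What the plan says.** The Statistical analyses section names the terms of the primary model: "including fixed effects for group, time, the group-by-time interaction and a random subject effect". It then says what the model is for: "GLMM analyses examine changes from baseline to each follow-up time point for each intervention group compared to the control group". Baseline is therefore part of the outcome vector, and the arms may have different baseline means. The section mentions neither a baseline covariate nor an equal-baseline constraint.

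The Sample size section uses the same contrast. The trial is sized on change in MVPA, with d = "0.45; corresponding with a minimal detectable difference of 10 min/day", at the "primary time point of 6 months". It concludes that "76 participants per group will be required to achieve 80% power using an alpha level of 0.05", and then: "The number of participants per group will be inflated by 30% (99 participants per group) to account for drop out".

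The Procedure section fixes the order of events. Participants are randomised only after baseline monitoring and the baseline survey are complete, and anyone with fewer than four valid monitoring days is excluded beforehand. Every randomised participant therefore has a baseline MVPA value that allocation cannot have affected.

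**The concern.** With group, time and their interaction all free, the 6-month interaction coefficient is the difference between arms in mean change from baseline. That subtracts the whole observed baseline difference from the 6-month difference. Because baseline precedes randomisation, the observed baseline difference is chance alone. Subtracting all of it is optimal only if a participant's 6-month value moves one for one with the baseline value. When rho is below 1 and variances are similar, the regression slope is below 1, so the change score overcorrects and adds noise.

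What is at stake is the precision of the primary estimate. The article reports recruitment as complete, so precision can no longer come from more participants under this plan, but the choice of analysis can still supply some.

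**Working it through.** **Inputs from the article.** Effect 10 min/day; d = 0.45 on change, so the SD of change is 10/0.45 = 22.2 min/day; 76 per arm before inflation and 99 after; 30% dropout; 80% power; alpha 0.05; 1:1 allocation; visits at baseline, 3 and 6 months.

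**Assumptions.** A two-sided test (sidedness is not stated; one-sided would need only 62 per arm). Rho from 0.5 to 0.9. Equal variances over time, an identity link and the compound-symmetric covariance that a random subject effect implies. In the dropout calculation, 15% missing at 3 months. The SD of change is held at 22.2 throughout, so that only the analysis varies.

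**1. The plan's own figure.** n per arm = 2 × (1.960 + 0.842)² / 0.45² = 77.5, so 78. With an SD of change of 22, n = 2 × (1.960 + 0.842)² × (22/10)² = 76. The stated 76 is therefore reproduced as a two-sample comparison of change scores, and 76 × 1.3 = 98.8, so 99.

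**2. The stated model with complete data.** The standard error of the 6-month interaction is 22.2 × √(2/76) = 3.605 min/day, the same as for a two-sample comparison of change. Power is 79.2%. The model and the sample size agree.

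**3. Variance ratio.** With visit SD σ:
- change contrast: 2σ²(1 − rho) × 2/n
- baseline-adjusted or common-baseline contrast: σ²(1 − rho²) × 2/n
- ratio: (1 − rho²) / [2(1 − rho)] = (1 + rho)/2

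This is 0.75, 0.80, 0.85, 0.90 and 0.95 at rho 0.5, 0.6, 0.7, 0.8 and 0.9. With 76 complete per arm, power moves from 79.2% to 89.3%, 87.3%, 85.3%, 83.2% and 81.2%.

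**4. The mixed model with the planned dropout.** Standard errors come from the generalised least squares information matrix with 99 per arm: 70% have all three visits, 15% have baseline and 3 months, and 15% have baseline only. Power = Φ(10/SE − 1.960). For example, at rho 0.5, 10/3.602 − 1.960 = 0.816 gives 79.3%, and 10/3.237 − 1.960 = 1.129 gives 87.1%.

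| rho | SE, stated model | SE, common baseline | Variance ratio | Power, stated | Power, common baseline |
|---|---|---|---|---|---|
| 0.5 | 3.602 | 3.237 | 0.808 | 79.3% | 87.1% |
| 0.6 | 3.621 | 3.334 | 0.848 | 78.9% | 85.1% |
| 0.7 | 3.640 | 3.428 | 0.887 | 78.4% | 83.1% |
| 0.8 | 3.657 | 3.518 | 0.925 | 78.1% | 81.1% |
| 0.9 | 3.675 | 3.606 | 0.963 | 77.7% | 79.2% |

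The ratios lie closer to 1 than in step 3 because, under dropout, the stated model already draws some information from incomplete records.

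**5. Unequal variances.** If the 6-month SD is k times the baseline SD, the complete-data ratio becomes k²(1 − rho²) / (1 + k² − 2 × rho × k). With an assumed k = 1.2:
- rho 0.6: 0.9216/1.00 = 0.92
- rho 0.7: 0.7344/0.76 = 0.97
- rho 0.8: 0.5184/0.52 = 0.997

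At rho 0.8 almost nothing is gained.

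**The case against.** The strongest reply is that nothing here is wrong. The stated model is a standard one, unbiased over randomisation; it matches the hypothesis of increased MVPA against control; and the sample size was built on the same contrast. The article is condensed and introduces the model terms non-exhaustively, so an analysis plan that is not shown could add a baseline term. The size of the gain also rests on a correlation and a variance pattern that the article does not give. Participants are selected for inactivity, so baseline spread may well be narrower than follow-up spread.

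Most of this stands, and it limits the point to efficiency. It does not remove it: the article names the main terms and the contrast, and as named they leave the baseline difference free.

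Three stronger readings are tempting, and the documents do not support them.

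- A reader might infer that chance baseline imbalance biases the result. In a given sample it does shift a change-score estimate, but over repeated randomisation that shift is the same extra variance already counted above. It is not a second harm.
- A reader might put the trial at about 75% power by testing change in 69 completers per arm (99 × 0.7). That is a completers-only t-test (74.7%). The plan is a mixed model that, where possible, includes everyone with valid baseline data, and under the dropout pattern above it gives about 78% to 79% at rho 0.5 to 0.8.
- A reader might say that adjustment restores 80% power. It does so in the table at rho 0.5 to 0.8 but not at rho 0.9 (79.2%), and unequal variances can remove most of the gain.

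Multiplying by 1.3 rather than dividing by 0.7 to allow for dropout is a separate sample-size matter and should be judged separately.

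**Conclusion.** The point holds as a matter of precision. The stated analysis is valid and consistent with its sample size, but it estimates a baseline difference that the design makes zero in expectation, and so gives away information already collected. Under the dropout pattern assumed above, the gain in power is about 8 points at rho 0.5, 6 at 0.6, 5 at 0.7, 3 at 0.8 and 1 to 2 at 0.9.

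These figures rest on the assumed rho, equal variances, an identity link and the assumed 15% loss at 3 months. With another link the contrast is still change from a free baseline, but (1 + rho)/2 is only approximate. The direction is secure: in large samples, baseline adjustment with a freely estimated slope is never less efficient than the change score. The size is not secure.

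**What to change.** Before the blinded analysis, prespecify one of two forms for the primary analysis:

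- a longitudinal model of all three visits with a common baseline mean: fixed effects for time, group at 3 months and group at 6 months, no group effect at baseline, and the random subject effect retained; or
- a model of the 3- and 6-month values with baseline MVPA as a covariate.

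The first keeps participants who have only a baseline record in the likelihood. Name the adjusted 6-month difference in min/day, with its confidence interval, as the primary result. Treat secondary outcomes measured at baseline in the same way.

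The cost is a change of wording and model coding. No new data are needed, since a valid baseline recording is a condition of entry. The constrained model has one parameter fewer than the stated one, and the covariate form spends one degree of freedom on baseline. Fixing the choice now also means that adjustment cannot appear to have been chosen after the results were seen. Describe it as a gain in precision, without promising a particular power.

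### The primary model's only stated within-person structure is a random subject effect; if MVPA correlation falls with time, the 6-month standard error would be too small

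*Protocol article*

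**What the plan says.** The Statistical analyses section of the protocol article sets out a generalised linear mixed model with group and time as fixed effects, together with "the group-by-time interaction and a random subject effect". It gives the target of that model as follows: "GLMM analyses examine changes from baseline to each follow-up time point for each intervention group compared to the control group". Dependence between a participant's measurements is mentioned once more, in the words "while accounting for within-person nesting of variables across time". The section names no residual covariance structure, no random slope and no robust standard error.

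The Trial design section sets the visits: "Primary and secondary outcomes will be assessed at baseline, 3 months and 6 months". The Sample size section bases the calculation on change in device-measured MVPA and places the powered comparison "at the study’s primary time point of 6 months". The article states no within-person correlation of MVPA, for any pair of visits.

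**The concern.** A random subject effect with independent residuals of constant variance implies compound symmetry: the same variance at every visit and the same correlation for every pair of visits. With three visits, the fitted common correlation is in effect the average of the three pairwise correlations.

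The primary contrast depends on one of those pairs only, baseline and 6 months, which is the most widely separated. If correlation declines as the gap widens, the average exceeds the 0–6 month value. The model then credits the primary contrast with more within-person precision than it has. Its confidence interval would be too narrow and its p-value too small, and this is the one comparison the trial is powered for. The estimate itself is not the issue; with complete data the problem lies in the standard error.

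**Working it through.** **The plan's own figure.** Inputs from the Sample size section: d = 0.45, 10 min/day, 80% power, alpha 0.05 (taken as two-sided), 76 per group.

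- n per group = 2 × (1.960 + 0.842)² / 0.45² = 77.5, so 78. The stated 76 is close; it gives 79.2% power by the normal approximation.
- If d is standardised by the SD of change, that SD is 10 / 0.45 = 22.2 min/day.
- This calculation uses no correlation between visits, so it does not reveal which correlation pattern was expected.

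**Formula.** Let ρ03, ρ36 and ρ06 be the pairwise correlations, with equal variances σ² at the three visits and complete data.

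- True variance of the between-group difference in change to 6 months, n per group: (2/n) × 2σ²(1 − ρ06).
- Variance reported under the random-subject-effect model: (2/n) × 2σ²(1 − ρ̄), where ρ̄ = (ρ03 + ρ36 + ρ06)/3.
- Ratio of reported to true standard error: r = √[(1 − ρ̄)/(1 − ρ06)].
- Actual two-sided type I error: 2 × [1 − Φ(1.96 r)].
- For the 3-month contrast, replace ρ06 by ρ03 in the denominator.

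**Worked example, 0.70/0.70/0.60.** ρ̄ = 2.00/3 = 0.667. r = √(0.333/0.400) = 0.913. 1.96 × 0.913 = 1.789, and the two-sided tail area is 7.4%.

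**Range.** All correlations below are assumptions.

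| ρ03 / ρ36 / ρ06 | ρ̄ | r, 6 months | Type I error, 6 months | Type I error, 3 months |
|---|---|---|---|---|
| 0.70 / 0.70 / 0.70 | 0.700 | 1.000 | 5.0% | 5.0% |
| 0.70 / 0.70 / 0.68 | 0.693 | 0.979 | 5.5% | 4.8% |
| 0.70 / 0.70 / 0.65 | 0.683 | 0.951 | 6.2% | 4.4% |
| 0.70 / 0.70 / 0.60 | 0.667 | 0.913 | 7.4% | 3.9% |
| 0.70 / 0.70 / 0.50 | 0.633 | 0.856 | 9.3% | 3.0% |
| 0.80 / 0.80 / 0.65 | 0.750 | 0.845 | 9.8% | 2.8% |

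The 3-month contrast is conservative here because ρ03 lies above the average. That is not guaranteed: with 0.60/0.75/0.55 both contrasts are too liberal (7.7% at 6 months, 6.1% at 3 months).

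**On the outcome scale.** With SD of change 22.2 min/day and 76 per group, the true standard error is 22.2 × √(2/76) = 3.60 min/day, a 95% half-width of 7.1 min/day. The model would report 0.913 × 7.1 = 6.5 min/day under 0.70/0.70/0.60, and 0.845 × 7.1 = 6.0 min/day under 0.80/0.80/0.65.

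**Simulation check.** With 76 per arm, complete data and no treatment effect (20,000 trials), the random-subject-effect analysis rejected in 7.3%, 9.0% and 9.8% of trials for 0.70/0.70/0.60, 0.70/0.70/0.50 and 0.80/0.80/0.65. An unrestricted test of the 6-month change gave 5.2%, 4.9% and 4.9%. A no-decay control (0.60 throughout) gave 5.1% against 5.0%. A smaller set of REML fits with 99 per arm (2,000 runs each, so a Monte Carlo error of roughly half a percentage point) gave, for 0.70/0.70/0.60, 6.4% with no dropout and 7.1% with 30% dropout. For no decay at 0.70 it gave 4.9% and 5.4%.

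**The case against.** The strongest reply is that a random subject effect does not by itself impose equal correlation. That also needs independent, equal-variance residuals and model-based standard errors, and the article states neither. Covariance structure and standard-error method are often left to a statistical analysis plan, and none is shown here. One of the remedies below would leave the model sentence untouched. This much stands: the problem follows from the ordinary reading of the sentence, not from its literal words alone. It does not dispose of the point, because the article does more than stay silent. It names a specific random structure for the primary model, and on the ordinary reading that structure fits the primary contrast poorly if correlation decays.

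Second, the effect is conditional. The article gives no correlation, variance or pilot data. If within-person dependence mostly reflects a stable personal activity level plus week-specific noise, correlation would be nearly flat and type I error close to 5%. This stands in full. A reader might infer that the planned test has an inflated type I error, or that it reaches 9–10%; the article does not support either, and those figures are the upper end of an assumed range.

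Third, the distribution and link are not settled, since the section makes the choice of technique depend on checks of linearity and normality. The closed formula covers the Gaussian identity-link case only. Multiple imputation was not simulated, though it would not by itself alter the covariance assumed by the analysis model.

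Fourth, a random-intercept model for three visits is common practice, and the 3-month contrast may err in the safe direction. Both are true, but the Sample size section makes 6 months primary, so conservatism at 3 months does not offset the risk where it counts.

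**Conclusion.** The point holds in conditional form and should be addressed. On its usual reading, the stated model estimates one correlation for three pairs of visits and applies it to the most distant pair. If correlation falls with time, the 6-month standard error is understated: by about 5% for a fall from 0.70 to 0.65, about 9% for a fall to 0.60, and about 14–15% in the two strongest patterns. Type I error at 6 months correspondingly runs from 5% to about 10%, and nominal 95% intervals would cover about 90–95%.

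These figures rest on assumed correlations, equal variances over time, an identity link, independent residuals and model-based standard errors. Where the trial lies in the range cannot be known from the article. Nothing here shows that the treatment estimate is biased or that the plan's alpha is in fact exceeded.

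**What to change.** Add one sentence to the Statistical analyses section for the primary outcome, before any analysis by group. Either of these would do:

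- Replace the random-intercept-only structure with an unstructured covariance over baseline, 3 and 6 months, with small-sample degrees of freedom. This needs six covariance parameters (three variances, three correlations), which 198 participants can support.
- Keep the random subject effect and base inference on robust standard errors clustered on participant.

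In both cases, state that the 6-month between-group difference in change is estimated from that model.

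Design, sample size and data collection are unaffected, and both options are available in standard mixed-model software. The downside is four covariance parameters more than the two of the simpler model (first option), and a slightly less precise standard error if the correlation is in fact constant.
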